## Research Protocol

### Overview

**Rationale:** Individuals with type 2 diabetes (T2D) display reduced cardiorespiratory fitness, which is a strong predictor of premature mortality and T2D-related complications. Aerobic training (AT) enhances cardiorespiratory fitness and is a cornerstone in the management and treatment of T2D. Emerging data suggest that AT combined with blood flow restriction (AT+BFR) training could enhance cardiorespiratory fitness faster than typical AT in healthy individuals. However, the feasibility of AT+BFR in individuals with T2D and its impact on cardiorespiratory fitness have yet to be determined.

**Objectives:** The primary objective of this study is to test the feasibility of a 6-week AT+BFR training intervention in individuals with T2D. The secondary objective is to establish preliminary effect sizes for the efficacy of AT+BFR training in individuals with T2D compared to standard care AT (AT- stdCare).

**Study Design:** This study is a single-blind (investigator & statistical analyst), multi-site, randomized controlled pilot trial of a novel AT+BFR training intervention for individuals living with T2D, informed by patients with lived experience. Participants will be randomized 1:1 using variable permuted block sizes (stratified by sex and site) into AT+BFR or AT-stdCare groups with outcome measures assessed at baseline and 6 weeks.

**Intervention:** The intervention will consist of 6 weeks of AT+BFR. Participants will perform AT+BFR 3 times weekly for 21-32 minutes per session. A blood pressure cuff will be set at 60-80% of limb arterial occlusion with AT progressing to 96 minutes per week of treadmill walking performed at 40-50% of heart rate reserve (HRR).

**Control:** Participants in the AT-stdCare will perform 96 minutes per week of treadmill walking at 40-50% of HRR following the same schedule as AT+BFR, training 3 times per week for 21-32 minutes per session.

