**Outcomes:** The main outcome measures will pertain to the feasibility of a larger trial and include recruitment rates, enrollment and adherence to the intervention, and retention for follow-up testing. The secondary outcomes will be focused on establishing effect sizes to power a larger trial. Effect sizes for changes in cardiorespiratory fitness and continuous glucose monitoring (CGM) outcomes will be determined to help select and power a primary outcome for a more definitive trial of AT+BFR. Exploratory outcomes will include quality of life measured with the American Diabetes Association Mental Health Tool Kit, sleep quality using the Pittsburgh sleep questionnaires, and dietary habits using the ASA24 self-administered 24-hour diet recall.

**Impact:** This study will be the first feasibility trial to test blood flow restriction as a strategy to augment the effects of exercise in individuals with T2D and could establish BFR training as a novel therapeutic modality for this population. Findings will determine if a larger, more definitive efficacy trial is warranted and will inform exercise specialists of an innovative exercise alternative to maximize the benefits of exercise in individuals living with T2D.

**Background:** The global burden of diabetes continues to grow at an alarming rate, with over 500 million people affected worldwide and projections indicating a 150% increase by 2050^1. In Canada, approximately 6 million individuals live with diabetes, with type 2 diabetes (T2D) accounting for over 90% of all cases. Diabetes is the seventh leading cause of death in Canada, reduces lifespan by 5 to 15 years and incurs lifetime direct treatment costs exceeding \$125,000 in adults, placing immense strain on both the healthcare system and population health. In light of its impact on morbidity, mortality, and healthcare resources, there is an urgent need for novel strategies that optimize T2D management and reduce long-term expenditures.

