To address this challenge, novel approaches that enhance the physiological stimulus of exercise without increasing the overall volume or intensity are urgently needed. Blood flow restriction (BFR) training has emerged as an innovative modality of exercise that may present a promising strategy to optimize exercise prescriptions for T2D management. BFR involves the application of controlled pressure to the limbs during exercise using a tourniquet system to partially restrict arterial inflow and occlude venous return, which amplifies metabolic stress and local hypoxia, contributing to physiological adaptations. While originally used in healthy and athletic populations, emerging evidence supports its safety and efficacy in clinical populations with neurological and musculoskeletal disorders. When combined with resistance or aerobic exercise, BFR enhances both muscular and cardiovascular adaptations at significantly lower intensities than traditional training. Similarly, aerobic activity performed at low-to-moderate intensity combined with BFR has been shown to augment improvements in cardiorespiratory fitness compared to aerobic exercise alone, with some data suggesting an 8% increase in cardiorespiratory fitness after only two weeks of aerobic BFR training. Altogether, in the context of T2D, BFR is an exciting avenue as it has the capacity to increase skeletal muscle mass, the main site of glucose uptake, and increase cardiorespiratory fitness. However, to the best of our knowledge, no trials have examined the feasibility or efficacy of treadmill-based aerobic training + BFR training in individuals of both sexes living with T2D.

Given the impaired cardiorespiratory fitness, blunted responsiveness to standard aerobic training, and elevated cardiometabolic risk in this population, BFR may offer a novel and practical method to amplify exercise adaptations without exceeding tolerable workloads.

**Objective:** The primary objective of this pilot trial is to test the feasibility of a six-week moderate-intensity aerobic training (AT)+BFR intervention in individuals living with T2D. The secondary objective is to establish effect sizes for the efficacy of AT+BFR compared to AT standard care (AT-stdCare) for changes in cardiorespiratory fitness, glycemia, and quality of life measures in individuals living with T2D.

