**Recruitment:** Participants (n = 60; n = 20 per site) will be recruited using social media and radio advertisements, and advertisements placed in pharmacies, healthcare centers, physician offices, and community organizations. Further recruitment will occur through electronic communication, including e-newsletters within various organizations and groups. Participants from previous studies who expressed interest in being considered for future research will also be contacted.

**Intervention:** The intervention will involve 6 weeks of treadmill-based aerobic exercise at 40-50% of heart rate reserve (HRR). The AT+BFR participants will perform the treadmill-based aerobic exercise with BFR cuffs inflated around the proximal thigh at 60-80% of their individualized limb occlusion pressure (LOP) determined at rest using an automated BFR tourniquet system (PTSi, Delfi Medical Innovations Inc. Vancouver, Canada). The percentage of LOP will progressively increase over the course of the intervention. Weeks 1 and 2 will be completed at 60% LOP, after which pressure will increase by 5% each subsequent week, corresponding to 65%, 70%, 75%, and 80% LOP during weeks 3, 4, 5, and 6, respectively. The BFR cuffs will remain inflated throughout the exercise protocol, but will deflate for 1 minute every 10 minutes as per safety/tolerability recommendations. The AT-stdCare participants will follow the same training schedule and progression as the AT+BFR group without using BFR cuffs during the exercise sessions. Participants will be eased into the program using a 1-week progressive start; they will complete 63 minutes of exercise in Week 1, split across 3 sessions (21 mins/session). For the remaining 5 weeks, participants will complete 96 minutes of exercise split across 3 sessions per week (32 mins/session). Each exercise session will begin with a five-minute warmup to achieve target intensity and end with a five-minute cool down, neither of which will be counted in the total exercise time. All exercise sessions will be supervised by research staff and take place in a private exercise facility located at each site. To maximize adherence to the intervention, exercise sessions are scheduled on a weekly basis with research staff available 7 days a week.

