| Continuous Glucose Monitor                                |   | X |                                                                                                                                                                                 | X  |    |

**Primary Outcome:** The primary outcome of the BOOST-HEALTH Trial is feasibility of a larger definitive trial. Primary selected end-points used to determine feasibility will include: 1) recruitment rates defined as the number of individuals inquiring about the trial, 2) enrollment rates defined as the number of participants who consent to participate in the trial and are randomized to one of the two study arms, 3) adherence to the intervention arms defined as the number of sessions each participant attended during the trial, 4) retention for follow-up testing defined as the number of participants who complete all post-testing measurements after the intervention, and 5) adverse events defined as any undesirable event occurring during the study. We will aim to recruit at least 1 participant per month per site, achieve >70% adherence, retain >80% of participants for follow-up testing, and minimize any adverse events related to BFR or AT.

**Secondary Outcomes:** *Cardiorespiratory fitness* ( $VO_{2peak}$ ) will be assessed using a modified Balke and Ware treadmill test protocol. Participants will walk at self-selected speed between 4.5-5.5 kilometers per hour (km/h) at a 0% grade on a motorized treadmill. After 2 minutes, the grade will be increased to 5.0% for 2 minutes, and then progressively increase by 1% every minute until a maximum grade of 15% is achieved. If a participant reaches the maximum grade, then speed will increase by 0.8 km/h each minute until volitional fatigue. Gas exchange will be continuously monitored using a metabolic cart, heart rate data will be obtained throughout the test using a Polar FT1 heart rate monitor (Polar, Kempele, Finland), and blood pressure data will be recorded every 2 minutes using an automated blood pressure monitor.  $VO_{2peak}$  will be identified as the average of the highest 30 seconds of  $VO_2$  observed during of the test.

*Glycemia* will be analyzed through glycated hemoglobin (HbA1c) via Abbott, Afinion™ 2 system analyzer. A finger prick will be conducted using a single-use lancet to collect a 1 microliter

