sample of whole blood. The sample will then be analyzed using a point of care analyzer where rapid assessment of HbA1c will be conducted and result provided in approximately 3 minutes. Blood glucose will also be continuously monitored (CGM) using commercially available CGM sensors (Abbott, FreeStyle Libre 3 Plus) for 15 days (7 days before the intervention starts and the first 8 days of the intervention). CGM data will be analyzed using the Diagnostics platform^59 yielding outcomes as described in the consensus for reporting of CGM data in trials.

*Quality of Life* will be assessed using validated self-report questionnaires. Health-related quality of life will be measured using the 36-Item Short-Form Health Survey (SF-36) while the diabetes-specific impacts on quality of life will be assessed using select questionnaires from the American Diabetes Association Behavioural Health Toolkit.

**Exploratory Outcomes:** At baseline, research staff will record participant self-reported demographics (age, sex/gender, ethnicity, socioeconomic status, and education), family medical history, T2D duration, and current medication usage. Participants will be monitored throughout the study and asked to report any changes in medication use to research staff as they occur. Medication usage and changes will be confirmed through detailed label inspection (of bottle or photo) or a pharmacy printout.

*Physiological and anthropometric measurements* will be taken over the span of two days, separated by less than one week. Participants' height, weight, blood pressure, heart rate, and hip and waist circumference will be measured by a member of the research staff according to the Canadian Society for Exercise Physiology protocols. Body composition, including fat mass, lean mass, and body fat percentage, will be estimated using dual-energy x-ray absorptiometry (DXA) following a 12-hour overnight fast.

*Blood samples* will be collected intravenously from the antecubital vein by a registered nurse or certified phlebotomist into 3mL Vacutainer collection tubes coated with an anticoagulant, ethylenediaminetetraacetic acid (EDTA). The blood samples will then be centrifuged at 1600g for 15 minutes (4°C) and the plasma aliquoted into 1.5mL microcentrifuge tubes for storage at -80°C until further analysis.

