*Dietary information* will be recorded using the Automated Self-Administered 24-Hour Dietary Assessment Tool (ASA24), reporting a weekday and weekend day at both baseline and post-testing to account for potential dietary intake variability. However, participants will be instructed to not change their dietary habits during the study.

*Sleep quality* will be measured at each time point using the Pittsburgh Sleep Quality Index (PSQI).

**Blinding:** To maintain single blinding, principal and co-investigators and the statistician will be blinded to participant study groups for data analyses. It is not feasible to blind participants in this trial.

**Randomization:** Randomization of the intervention participants will occur following completion of the baseline testing visits. Participants will be randomized using a 1:1 allocation ratio with variable permuted block sizes (stratified by sex and site) through the web-based platform REDCap. A member of staff who is not related to the project and has no contact with participants will hold the password-protected randomizations. When a new participant completes baseline testing and is ready for randomization, the participants ID number, sex, and location will be sent to the member of staff with randomizations via email and they will respond to research staff with the randomization (AT+BFR or AT-stdCare.) for that participant.

**Sample Size Calculation:** There are no clear guidelines for calculating sample size for a pilot/feasibility trial. The sample size calculation was based on determining the feasibility of a larger trial and informed by control group and BFR group data from a study performed by one of our team members using cardiorespiratory fitness as a key efficacy outcome. The mean change in cardiorespiratory fitness for the control and the BFR training group were 1.3% + 4.8% and 8.7% + 7.3%, respectively, from which an effect size Cohen's d was calculated to be 1.2. To be more conservative, using an effect size of 0.25 and nominal type 1 (0.05) and type 2 (0.10) errors, our sample size was estimated to be a total of 46 (n = 23 per arm) for a repeated measure, within-between interaction (calculated using G\*Power v3.1). To account for a potential 25% dropout rate, which is typical for exercise trials, and missing data, a total sample size of n = 60 (n = 30 per arm; n = 20 per site) was selected.

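### The glycemia text describes one CGM wear ending on training day 8, whereas Table 1 also marks CGM in week 9; the follow-up wear and its window need to be written into the text

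*Protocol*

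**What the plan says.** Four places in the Protocol bear on when CGM is measured and what it is for.

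- **Methodology, Secondary Outcomes (Glycemia):** CGM is worn "for 15 days (7 days before the intervention starts and the first 8 days of the intervention". No second wear is described. HbA1c is listed in the same paragraph as the other glycemia measure.
- **Table 1:** the row "Continuous Glucose Monitor" has a mark at visit 2 (week 2) and another at visit 21 (week 9). Training fills weeks 3 to 8 (visits 3 to 20). The table gives no wear length and does not say whether a mark means sensor placement or data collection.
- **Overview, Outcomes:** "Effect sizes for changes in cardiorespiratory fitness and continuous glucose monitoring (CGM) outcomes will be determined", so as to help select and power the primary outcome of a definitive trial. The Study Design paragraph describes a trial "with outcome measures assessed at baseline and 6 weeks", and the Objective asks for effect sizes "for changes in cardiorespiratory fitness, glycemia, and quality of life measures in individuals living with T2D".
- **Methodology, Intervention:** training starts gently. For the first week, "they will complete 63 minutes of exercise in Week 1, split across 3 sessions (21 mins/session"). Weeks 2 to 6 have three 32-minute sessions each. In the AT+BFR arm, cuff pressure is 60% of limb occlusion pressure in weeks 1 and 2, then rises in steps to 80% in week 6.

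On allocation, the Randomization paragraph says: "Randomization of the intervention participants will occur following completion of the baseline testing visits".

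**The concern.** The 15 days in the text are fully used by the week before training and the first eight days of it. A site that follows the text would place one sensor and collect nothing at follow-up. The only change then available compares the pre-training week with the start of training, when session length and cuff pressure are at or near their lowest. That answers a different question from the 6-week effect, and CGM is one of the two outcomes named for choosing and powering the next trial. Sensor data that were never collected cannot be recovered in the analysis, so a later statistical analysis plan cannot repair this.

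The conflict also reaches a primary feasibility endpoint. Retention counts participants who complete all post-testing measurements, with a target above 80%. Under Table 1, CGM is one of those measurements; under the text, it is not. The numerator therefore depends on which place is read.

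With three sites of 20 participants each, the ambiguity also leaves room for sites to collect different windows.

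**Working it through.** **Inputs.** Wear of 7 + 8 days (Secondary Outcomes, Glycemia). Training in weeks 3 to 8, visits 3 to 20, with CGM marks in weeks 2 and 9 (Table 1). Three sessions a week, 63 minutes in week 1 and 96 minutes a week in weeks 2 to 6, and the cuff-pressure steps (Intervention).

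**1. The stated wear length.** 7 + 8 = 15 days, as the Protocol says. Nothing is left over for follow-up.

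**2. Position on the calendar.** Training lasts 6 × 7 = 42 days, with day 1 at the start of week 3. The described wear ends on day 8, so it reaches 8/42 = 19% of the training period and stops 42 − 8 = 34 days before training ends.

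**3. Sessions covered.** The total is 6 × 3 = 18, which agrees with visits 3 to 20. Days 1 to 7 hold the three week-1 sessions. Day 8 may hold the first week-2 session, assuming at most one session a day. Coverage is therefore 3/18 = 16.7% to 4/18 = 22.2%.

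**4. Minutes covered.** The planned total is 63 + 5 × 96 = 543 minutes. Covered are 63/543 = 11.6%, or with a day-8 session (63 + 32)/543 = 95/543 = 17.5%.

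**5. Cuff pressure covered.** Weeks 1 and 2 are at 60%. Weeks 3 to 6 hold 4 × 3 = 12 sessions at 65% to 80%. The described wear sees 0 of those 12.

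**6. Can one wear explain both Table 1 marks?** Week 9 begins on intervention day 43, and the described wear ends on day 8. The visit 21 mark therefore needs a second wear, which the text does not contain.

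**7. The two places side by side.**

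| | Glycemia text | Table 1 |
|---|---|---|
| CGM periods | One | Two |
| Baseline | 7 days before training | Mark at visit 2, week 2 |
| Later data | Training days 1 to 8 | Mark at visit 21, week 9 |
| Contrast available | Early response | Baseline to follow-up, window undefined |
| CGM is a post-testing measurement | No | Yes |

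The baseline halves fit together: a sensor placed in week 2 can supply 7 days before training starts in week 3. If the mark means placement at visit 21 as well, the follow-up window lies wholly after the last session. If it means collection, the window lies before visit 21. The Protocol does not settle which.

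**The case against.** The strongest reply is that Table 1 already schedules the follow-up CGM. The Overview sets outcomes at baseline and 6 weeks, and the Data Collection paragraph describes two post-testing visits. On that reading the text merely omits the second wear, and one added sentence cures it. This stands in large part. A reader might infer that the Protocol contains no CGM measure of the 6-week effect at all; the Table 1 mark rules that out. What remains is that the only wear actually described excludes follow-up, and the one that is marked has no length or window.

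Several further inferences are tempting but go beyond the documents:

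- **That the glycemia objective is unserved.** It is not, because HbA1c is also a glycemia outcome. HbA1c does not, however, supply the CGM effect sizes that the Overview promises.
- **That a week-9 window is itself a defect, or that the last training week is the right one.** Table 1 places the other post-testing measurements after training too (cardiorespiratory fitness is at visit 22), so a post-training CGM window is consistent with that design. A window during training would be a different estimand, and the documents give no ground for preferring it.
- **That the early contrast would be reported as the 6-week effect, or that sites would diverge.** Both are possible results of the ambiguity. The Protocol states neither.
- **That participants know their arm during the 7 baseline CGM days.** Randomisation follows the baseline visits, visit 2 is the last of them, and participants are not blinded, so this can happen. The Protocol gives no date for randomisation or disclosure relative to those days, so it is not established.

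It is also fair to say that the primary outcome is feasibility and that the sample size rests on cardiorespiratory fitness. No sample size, power or alpha figure is affected.

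**Conclusion.** The point holds as an internal contradiction with a practical consequence. Followed to the letter, the Glycemia text would yield CGM data only up to day 8 of 42, with no exposure to the 12 sessions above 60% of limb occlusion pressure, and so only an early-response contrast. Table 1 shows that a follow-up measurement is intended, so the conclusion is not that the trial lacks one. It is that the Protocol states the CGM schedule in two incompatible ways and defines the follow-up window in neither.

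The session and minute counts assume that training starts on the first day of week 3, that all sessions take place as planned, and that at most one session falls on day 8. The contradiction itself depends on none of these. Calling the follow-up window post-training assumes that the Table 1 mark at visit 21 means sensor placement.

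**What to change.** Amend the Glycemia text and Table 1 so that they agree:

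1. Add the second, follow-up wear to the text, with its length and its window relative to the last training session, the same at all three sites. State in Table 1 whether a mark means placement or collection.
2. Define the CGM endpoint as the change from the 7 pre-intervention days to that follow-up window, and label the window for what it is: post-training if the sensor is placed at visit 21.
3. Report the first 8 training days only as an early-response measure.
4. State whether the follow-up CGM is among the post-testing measurements that count towards retention.

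Optionally, state that allocation is disclosed only after the 7 baseline CGM days, since the current text allows it to be known during them.

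The cost is an amendment and, if the Table 1 wear is not already budgeted, one more sensor per participant (up to 60 at the planned sample size). The change should be made before further follow-up windows pass, because missed sensor data cannot be collected later.
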